## Abstract

**Background:**

There have been few randomized control trials comparing the incidence of stent fracture and primary patency among different self-expanding nitinol stents to date. The SMART™ CONTROL stent (Cordis Corp, Miami Lakes, Florida, United States) has a peak-to-valley bridge and inline interconnection, whereas the COMPLETE™-SE stent (Medtronic Vascular, Santa Rosa, California, United States) crowns have been configured to minimize crown-to-crown interaction, increasing the stent's flexibility without compromising radial strength. Further, the 2011 ESC (European society of cardiology) guidelines recommend that dual antiplatelet therapy with aspirin and a thienopyridine such as clopidogrel should be administered for at least one month after infrainguinal bare metal stent implantation. Cilostazol has been reported to reduce intimal hyperplasia and subsequent repeat revascularization. To date, there has been no randomized study comparing the safety and efficacy of two different antiplatelet regimens, clopidogrel and cilostazol, following successful femoropopliteal stenting.

**Methods/Design:**

The primary purpose of our study is to examine the incidence of stent fracture and primary patency between two different major representative self-expanding nitinol stents (SMART™ CONTROL versus COMPLETE™-SE) in stenotic or occlusive femoropopliteal arterial lesion. The secondary purpose is to examine whether there is any difference in efficacy and safety between aspirin plus clopidogrel versus aspirin plus cilostazol for one month following stent implantation in femoropopliteal lesions. This is a prospective, randomized, multicenter trial to assess the efficacy of the COMPLETE™-SE versus SMART™ CONTROL stent for provisional stenting after balloon angioplasty in femoropopliteal arterial lesions. The study design is a 2x2 randomization design and a total of 346 patients will be enrolled. The primary endpoint of this study is the rate of binary restenosis in the treated segment at 12 months after intervention as determined by catheter angiography or duplex ultrasound.

**Discussion:**

This trial will provide powerful insight into whether the design of the COMPLETE™-SE stent is more fracture-resistant or effective in preventing restenosis compared with the SMART™ CONTROL stent. Also, it will determine the efficacy and safety of aspirin plus clopidogrel versus aspirin plus cilostazol in patients undergoing stent implantation in femoropopliteal lesions.

**Trial registration:**

Registered on 2 April 2012 with the National Institutes of Health Clinical Trials Registry (ClinicalTrials.gov identifier# NCT01570803).

## Background

Percutaneous transluminal balloon angioplasty for atherosclerotic femoropopliteal lesions has a high primary success rate of 90% without complications. However, restenosis rates are 60% within a year and restenosis rates increase to 70% for interventions on the superficial femoral artery where the lesion length is over 10 cm. Because of this, surgical treatment for restenosis was recommended by the Inter-Society Consensus for the Management of Peripheral Arterial Disease (TASC) in 2000 [1]. Later, a stainless steel stent was developed for atherosclerotic femoropopliteal lesions and adopted for clinical use. However, five randomized controlled trials failed to demonstrate any benefit of a stainless steel stent over balloon angioplasty alone [2–6].

The development of a nitinol stent has resulted in an innovative change in the interventional approach. Nitinol stents have contributed greatly to the lowering of restenosis rates and have also been shown to be superior to balloon angioplasty alone [7–10]. Based on these findings, the TASC II practice guidelines were developed [11]. Due to the development of the nitinol stent, restenosis rates have been reduced following femoropopliteal stenting. However, the use of a nitinol stent is only recommended when the result of a balloon angioplasty is not satisfactory as the ‘provisional concept’, and restenosis rates are still high in long lesions, such as TASC type C and D lesions.

The superficial femoral artery is the longest artery in human body and is located between two flexion points, the femoral joint and knee joint. Several types of forces are regularly applied to this vessel, such as flexion, longitudinal or lateral compression, torsion and others. Because of such features of the femoropopliteal artery, stent fracture can occur and several studies reported that the stent fracture can be a clinically significant factor in restenosis [12, 13].

Other reported risk factors for in-stent restenosis include stent length and the number of implanted stents (overlapping stenting), stent design, severity of calcification of the vessel, and stent elongation that may occur during deployment [14, 15]. Recently developed stent designs focus on reducing the rate of stent fracture to prevent restenosis. In the FESTO study [12], it was hypothesized that differences in nitinol stent designs affect stent fracture and restenosis rates. In this study, the Luminexx stent showed the highest stent fracture rate while the SMART™ stent showed the lowest stent fracture rate, with the fracture rate increasing with lesion length. Additionally, it was concluded that stent fracture is closely related to in-stent restenosis or reocclusion. Based on an *in vitro* study, Stefan Müller-Hülsbeck *et al*. claimed that there are differences in the performance of seven different types of stents in a mechanical fatigue test designed to predict stent fracture and, based on this, they also claimed that differences in stent design may play an important role in development of stent fracture [16].

Currently, several manufacturers produce nitinol stents for atherosclerotic femoropopliteal lesions, and all of them may differ in incidence of stent structure. As mentioned earlier, there are several laboratory, retrospective, or registered clinical studies on restenosis that compare the effect of bending, compression, and torsion on stent fracture rates in a variety of stent designs or types. However, well-designed, prospective, randomized, controlled clinical trials that compare restenosis rates among different stent types have rarely been conducted. Until now, the SUPER-SL study [14] is the only literature available for a randomized comparative study examining differences in primary patency rates between the SMART™ stent and Luminexx stent in long superficial femoral artery lesions (lesion length 5 to 22 cm). There is no randomized comparative study that compares two different types of nitinol stents in terms of stent fracture and primary patency rates in an Asian population, especially among new-generation nitinol stents.

The SMART™ CONTROL stent (Cordis Corp, Miami Lakes, Florida, United States) and the COMPLETE™-SE stent (Medtronic Vascular, Santa Rosa, California, United States) are both open-cell slotted tube designs, but they differ in connection shape between cell and cell or between crown and crown, and number of bridges. Because of such differences in design, Medtronic claim that the COMPLETE™-SE stent has exceptional elasticity and flexibility compared to other nitinol stents, without decreasing radial force.

Further, according to the 2011 ESC (European society of cardiology) guidelines [17], dual antiplatelet therapy with aspirin and clopidogrel is recommended at least for one month after the implantation of a bare metal stent into an atherosclerotic femoropopliteal lesion. Clinical research on the effectiveness of cilostazol in atherosclerotic peripheral arterial disease have been frequently reported. Recently, meta-analysis results have also reported that cilostazol is effective in reducing intermittent claudication [18]. However, while there are small-scale [19] or retrospective studies [20] that include a partial comparison showing a reduction in restenosis or revascularization rates in patients stented for femoropopliteal artery disease, there are few studies involving a large number of patients. Additionally, there are no randomized studies comparing the long-term effects of clopidogrel and cilostazol on reducing restenosis or revascularization rates in patients following femoropopliteal artery self-expanding nitinol stenting.

In this study, we will compare the incidence of stent fracture and primary patency between SMART™ CONTROL and COMPLETE™-SE stents. In addition, we would like to ascertain whether there are differences in efficacy and safety between aspirin plus clopidogrel versus aspirin plus cilostazol in patients undergoing stent implantation in femoropopliteal lesions.

## Method/Design

### Study objectives, hypothesis and design

The primary purpose of our study is to examine and compare the incidence of stent fracture and primary patency between two different nitinol stents (SMART™ CONTROL versus COMPLETE™-SE) in stenotic or occlusive femoropopliteal arterial lesions. The secondary purpose is to ascertain whether there is difference in efficacy and safety between aspirin plus clopidogrel versus aspirin plus cilostazol in patients undergoing stent implantation in femoropopliteal lesions. This is a prospective, randomized, multicenter trial to assess the efficacy of the COMPLETE™-SE versus SMART™ CONTROL stent by provisional stenting after balloon angioplasty for stenotic or occlusive femoropopliteal arterial lesions. The protocol of the trial has been registered with the National Institutes of Health Clinical Trials Registry (registration number: NCT01570803) and a brief flow chart of the whole study is summarized in Figure 1.

**Figure 1 Fig1:**
[figure not shown]
**Flow chart of the enrolled patients.** ABI: Ankle-brachial index; PCI: Percutaneous coronary intervention.

### Study population

Patients at least 20 years of age who have moderate or severe intermittent claudication or critical limb ischemia (Rutherford score of 2 to 6, except any patient who has undergone or plans to take major amputation) will be screened for study enrollment. A patient will be enrolled if they meet all of the inclusion and have none of the exclusion criteria. Inclusion criteria consist of clinical and anatomical criteria. The clinical criteria includes symptomatic peripheral-artery disease with moderate to severe claudication (Rutherford score of 2 to 3), chronic critical limb ischemia with resting ischemic pain (Rutherford score of 4), or chronic critical limb ischemia with ischemic ulcers (Rutherford score of 5 to 6), and patient must provide written informed consent. The anatomical criteria includes stenosis of more than 50% of, or occlusion of the ipsilateral femoropopliteal artery, patent (≤50% stenosis) ipsilateral iliac artery, or concomitantly treatable ipsilateral iliac lesions (≤30% residual stenosis), and at least one patent (less than 50% stenosis) tibioperoneal run-off vessel. Patients meeting any of the following criteria will be excluded from the study: failure to provide written informed consent; a history of major bleeding within prior two months; known hypersensitivity or contraindication to any of the following medications: heparin, aspirin, clopidogrel, cilostazol, or contrast agent; acute limb ischemia; previous bypass surgery or stenting of the ipsilateral femoropopliteal artery; untreated inflow disease of the ipsilateral pelvic arteries (>50% stenosis or occlusion); patients who have undergone major amputation (amputation of above the ankle) or major amputation is planned or required; patients with a life expectancy of less than one year due to comorbidities.

### Randomization and interventions

Prior to the intervention, aspirin and clopidogrel will be administered at least 12 hours before the procedure. Prior to the intervention, 70 to 100 units/kg of unfractionated heparin will be administered. Endovascular interventions will be carried out percutaneously, by placing a 6–8-Fr sheath at the femoral artery via an antegrade approach or a contralateral crossover technique. In selected cases, a retrograde approach (from the distal superficial femoral artery, popliteal artery, or pedal arteries) and/or brachial approach will be allowed.

Diagnostic angiography will be performed in two different views at least 30 to 45° apart to evaluate the structure of the lesion. Femoropopliteal and tibial arteries will be visually checked for the presence of distal lesions. To document the precise location of the lesion and the site of the intervention, we will recommend the use of a ruler. In cases of total occlusion, both intraluminal and subintimal methods of recanalization will be allowed. In procedure, the use of other special devices will be allowed; for example reentry device OUTBACK™ catheter (Cordis Corp, Miami Lakes, Florida, United States) and Offroad catheter (Boston Scientific, Natick, MA, United states), CTO devices Frontrunner (Cordis Corp, Miami Lakes, Florida, United States) and Truepath (Boston Scientific, Natick, MA, United states), and atherectomy devices such as SilverHawk™ and TurboHawk™ (Covidien, Plymouth, Minnesota). After the successful passage of the guidewire, predilation of the target lesion with an optimally sized balloon will be performed prior to stent implantation. Recommended, minimal balloon dilation time is 120 seconds. Then, if there is a residual pressure gradient of ≥10 mmHg, residual stenosis of ≥30%, or flow-limiting dissection, the balloon angioplasty results will be considered as suboptimal results. Subsequently, web-based randomization for stent selection will be performed. Patients will be stratified into two groups, less than 15 cm or more than 15 cm, according to lesion length. Random allocation of the patients will be performed via a web-based computerized program separately managed at the Cardiovascular Intervention Research Institute (CIRI), Korea University Guro Hospital, Seoul, Republic of Korea. Patients will be randomized in a 1:1 manner according to two different stents (SMART™ CONTROL versus COMPLETE™-SE). The stents will be implanted to extend 10 mm proximally and distally from the margins of the target lesion with luminal narrowing of ≥50%. Spot stenting or full lesion coverage will be decided at physician’s discretion. When multiple stents are required, the margins of the stents should be overlapped by at least 10 mm. Adjuvant post-dilation after the stenting will be performed strictly within the stented segment, with up to 10% oversizing of the post-dilation balloon.

All ipsilateral iliac arterial lesions should be treated with angioplasty and/or stenting concomitantly and residual stenosis should be less than 50%. Treatment of tibioperoneal lesions is recommended only in cases of critical limb ischemia. There should exist at least one patent (<50% stenosis) tibioperoneal run-off vessel with good antegrade flow.

A final angiography will be performed after the intervention in both groups, with the use of the same angles and magnifications used in the baseline angiograms. Simultaneously, reference vessel diameter (RVD), minimal luminal diameter (MLD), percent diameter stenosis, and acute gain should be measured. The reference vessel diameter will be obtained from averaging 5-mm segments proximal and distal to the lesion. Technical success will be defined as the successful access and deployment of the stent and less than 30% diameter residual stenosis after the revascularization.

For the post-procedural medication, aspirin 100 mg and clopidogrel 75 mg will be administered once daily for one month. Then, patients of each group will be randomized by web-based randomization to receive either clopidogrel 75 mg or cilostazol 100 mg once daily in addition to aspirin 100 mg for at least 11 months in a 1:1 manner.

After enrollment and index procedure, clinical follow-up will be planned at 1, 6, and 12 months to evaluate clinical outcomes and ankle-brachial index score. Also, all patients will be recommended to have a follow-up catheter angiography or duplex ultrasound at 12 months according to local clinical practice. The incidence of stent fracture and binary patency will be assessed by plain X-ray and quantitative femoral angiography. The investigators will be urged to follow up on patients, either by office visits or by telephone contacts, as necessary. Patient adherence to the study drug and side effects will be checked and monitored at every outpatient visit. The decision of drug discontinuation will be discussed and checked under the physician’s recommendation.

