### Outcome measures

The primary endpoint of this study is the rate of binary restenosis (stenosis of at least 50% of the luminal diameter) or PSVR (peak systolic velocity ratio) ≥2.5 or 0 (PSVR = peak systolic velocity within the area of stenosis divided by peak systolic velocity in a normal adjacent proximal artery segment) in the treated segment at 12 months after the intervention as determined by catheter angiography or duplex ultrasound. The secondary endpoints are as follows: 1) composite of binary restenosis and major stent fracture (moderate or severe stent fracture); 2) stent fracture rate according to fracture grade (minor, moderate, severe); 3) limb salvage rate free of above-the-ankle amputation; 4) sustained clinical improvement rate at 12-month follow-up; 5) repeated target lesion revascularization (TLR) rate; 6) repeated target extremity revascularization (TER) rate; 7) total reocclusion rate; 8) comparison of angiograph variables consisting of late loss and restenosis rate; 9) ankle-brachial index (ABI) at 12 months; 10) the rate of major adverse cardiovascular events (MACE) composed of all-cause death, myocardial infarction, repeat percutaneous coronary intervention (PCI), and stroke at 12 months; 11) incidence of geographic miss during stent deployment due to jumping and/or elongation; 12) rate of binary restenosis or PSVR ≥2.5 or 0 according to clopidogrel and cilostazol; and 13) major bleeding rate between clopidogrel and cilostazol group. The detailed definitions are summarized in the Appendix.

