
In conclusion, we still do not know whether there is a difference in primary patency and stent fracture between two self-expandable nitinol stents with a different design (SMART™ CONTROL versus COMPLETE™-SE) in stenotic or occlusive femoropopliteal arterial lesions. Furthermore, the efficacy and safety between aspirin plus clopidogrel versus aspirin plus cilostazol in patients undergoing stent implantation in femoropopliteal lesions will be evaluated. We hope to address these issues in the SENS-FP trial, whereby we will enroll a large unselected population of patients treated with stent implantation for significant peripheral arterial disease.

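### The clopidogrel–cilostazol endpoints are not timed from the drug randomization, so events before assignment can count and dilute the comparison

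*Protocol article*

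**What the plan says.** All from the protocol article.

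- **Drug timing** (Randomization and interventions). After stenting, "aspirin 100 mg and clopidogrel 75 mg will be administered once daily for one month". The second randomization comes only after that month: "Then, patients of each group will be randomized by web-based randomization to receive either clopidogrel 75 mg or cilostazol 100 mg once daily". Both groups also take aspirin, allocation is equal, and the assigned drug is to be taken for eleven months or longer. The article attaches no condition to this second randomization.
- **Follow-up** (same section). "clinical follow-up will be planned at 1, 6, and 12 months to evaluate clinical outcomes and ankle-brachial index score". Duplex or angiography is recommended at month 12; none is planned at month 1.
- **Drug endpoints** (Outcome measures). Restenosis is read twelve months from the intervention. Secondary endpoint 12 splits the same measure by drug: "rate of binary restenosis or PSVR ≥2.5 or 0 according to clopidogrel and cilostazol". Secondary endpoint 13 is major bleeding by drug, with no time window.
- **Bleeding definitions** (Appendix, Bleeding and hemorrhagic complications). Some bleeding linked to the catheterization laboratory visit, up to discharge, is classed as major.
- **Analysis sets** (Statistical analysis). Intention-to-treat covers everyone assigned to a treatment group; a per-protocol analysis is also planned.
- **Stated objective.** The closing paragraph of the Discussion says "the efficacy and safety between aspirin plus clopidogrel versus aspirin plus cilostazol in patients undergoing stent implantation in femoropopliteal lesions will be evaluated". The abstract describes the comparison as "aspirin plus clopidogrel versus aspirin plus cilostazol for one month following stent implantation in femoropopliteal lesions", which does not agree with the drug period of at least 11 months.
- **Enrollment exclusion** (Study population). One exclusion is "a history of major bleeding within prior two months".

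**The concern.** A randomized comparison normally starts its outcome clock at, or after, the randomization that creates the groups. Here the groups are formed about one month after stenting, while the efficacy clock starts at stenting and the safety clock has no stated start. A stent that occludes in week 3 and is still occluded at month 12 is an endpoint 12 event in whichever drug group the patient later joins. A groin bleed before discharge can likewise be entered under a drug not yet assigned.

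Such events say nothing about the choice of drug. They add the same expected burden to both groups, shrink the visible difference and cost power in the trial's named secondary purpose. The stated objective also describes a different question from the one the design answers. After a month of clopidogrel for everyone, the contrast is between continuing it and changing to cilostazol, not between two regimens started at implantation.

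**Working it through.** **1. The plan's own figure.** Inputs from Sample size calculation: restenosis 35% versus 20% (patency 65% versus 80%), 5% significance level, 80% power, 20% dropout. The two-proportion formula with pooled variance under the null, two-sided, gives 138 per group; 138/0.80 = 172.5, rounded up to 173, and 2 × 173 = 346. The stated 138 and 346 reproduce. They concern the stent comparison; no sample size is given for the drug comparison.

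**2. How many patients could enter already failed.** The document gives no month-1 rate. Assume that a fraction f of the 12-month restenoses has occurred by month 1, equally in both future drug groups, and that all enrolled patients are drug-randomized.

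- Average restenosis: (0.35 + 0.20)/2 = 0.275.
- Expected cases: 346 × 0.275 ≈ 95.
- f = 5%, 10%, 20%: about 5, 10 and 19 patients, the extremes being 5/346 = 1.4% and 19/346 = 5.5% of patients.

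**3. Effect on the restenosis contrast.** Let e be the share of patients already failed at drug assignment. As an illustration, borrow 35% versus 20% for the two drugs among patients still patent at month 1, with 138 evaluable per arm. The observed rate in each arm is e + (1 − e)p, so the difference shrinks by the factor (1 − e). Power is Φ{[√n·|p₁ − p₂| − 1.96·√(2p̄(1 − p̄))] / √(p₁(1 − p₁) + p₂(1 − p₂))}.

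| e | Observed rates | Difference (points) | Risk ratio | Power, all counted | Power, early failures excluded |
|---|---|---|---|---|---|
| 0 | 35.0% vs 20.0% | 15.0 | 0.57 | 80.0% | 80.0% |
| 2% | 36.3% vs 21.6% | 14.7 | 0.60 | 77.1% | 79.2% |
| 5% | 38.3% vs 24.0% | 14.3 | 0.63 | 72.7% | 78.0% |

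The exclusion column uses 138(1 − e) per arm at 35% versus 20%.

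A second parametrization holds the higher overall rate at 35% and keeps the risk ratio at 0.57 among patients patent at month 1. Power is then 74.8% (77.0% with exclusion) at e = 2%, and 65.8% (72.0%) at e = 5%. Under either version, exclusion recovers about 2 points at e = 2% and 5 to 6 points at e = 5%.

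**4. Type I error.** With no drug effect, a common post-assignment rate of 27.5% and 138 per arm, 200,000 simulated trials rejected at 0.050 for e = 0 and 0.050 for e = 5%. Early failures do not create false positives.

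**5. Bleeding.** No rates are given. Purely for illustration, assume 2% versus 1% after assignment and an equal extra b before it. The absolute difference stays at 1 point, but the ratio (b + 0.01)/(b + 0.02) moves from 0.50 at b = 0 to 0.67, 0.75 and 0.80 at b = 1%, 2% and 3%.

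**The case against.** Much can be said on the other side.

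- **Re-check at month 1.** A reader might infer that every stented patient is drug-randomized with no check. The article does not say so. It condenses a fuller protocol, plans a month-1 clinical visit with ankle-brachial index, and has adherence and side effects reviewed at each outpatient visit. Silence on a checklist is no finding.
- **Bleeding exclusion.** A reader might see a direct contradiction between this exclusion and the month-1 randomization. The exclusion is written for enrollment. A patient who bleeds in month 1 would meet it only if it were applied again, and nothing says that such a patient must receive further dual therapy.
- **Re-treatment.** A lesion re-treated in week 3 is not automatically an endpoint 12 event. It counts only if restenosed at the 12-month reading, and target lesion revascularization is not listed as a drug-specific endpoint.
- **A tilt toward clopidogrel.** A reader might infer that the first month filters out clopidogrel intolerance and so biases safety. The article does not say what happens to patients who bleed or stop the drug in month 1. They cannot be both filtered out and re-randomized. Whoever is randomized is randomized after those events, which balance in expectation.
- **The question itself.** The Discussion's rationale names the lack of evidence on the best agent after the first month, so continuing versus switching is what the design is built to ask.

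All of this stands. It leaves untouched the fact that endpoint 12 is timed from the intervention and endpoint 13 from no stated date, while assignment comes a month later.

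**Conclusion.** The point holds in a limited form. The stated timing lets persistent month-1 failures, and procedural or other month-1 bleeds, count in the drug comparison. The consequence is dilution and lost power, not bias of one randomized drug group against the other; type I error stays at about 5%.

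In the illustration, power falls from 80% to about 77% and 73% at 2% and 5% early failure, with a larger fall under the alternative parametrization. The early-failure shares, their equality across groups and the borrowed 35% versus 20% are assumptions; the documents give no month-1 rates. The primary comparison and its 346 patients are unaffected. This is a worthwhile, inexpensive correction to a secondary comparison.

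**What to change.** 1. Count major bleeding in the drug comparison from the date of drug randomization.
2. Analyse endpoint 12 by drug in drug-randomized patients with no restenosis, occlusion or target lesion revascularization documented before drug assignment. Membership then depends only on information that precedes assignment, so the randomization is preserved. Keep all drug-randomized patients as a sensitivity analysis.
3. Report events before drug assignment separately. Excluded patients remain in the stent comparison.
4. Word the secondary objective and its conclusion as continuing clopidogrel versus switching to cilostazol after one month of aspirin plus clopidogrel, and reconcile the abstract's one-month description with the drug period in Randomization and interventions.
5. Reconcile the enrollment bleeding exclusion with the month-1 randomization by stating whether it applies at that step. Which clinical rule applies is for the sponsor to decide.

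**Cost.** Revised wording and slightly fewer patients in a secondary comparison. The recovery of power is partial: with no imaging planned at month 1, silent restenosis would go undetected and remain in the analysis.
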